## Abstract

**Background:**

Treatment of ST-elevation myocardial infarction (STEMI) has improved over the years. Current challenges in the management of STEMI are achievement of early reperfusion and the prevention of microvascular injury. Sonothrombolysis has emerged as a potential treatment for acute myocardial infarction, both for epicardial recanalisation as well as improving microvascular perfusion. This study aims to determine safety and feasibility of sonothrombolysis application in STEMI patients in the ambulance.

**Methods:**

Ten patients with STEMI will be included and treated with sonothrombolysis in the ambulance during transfer to the PCI centre. Safety will be assessed by the occurrence of ventricular arrhythmias and shock during sonothrombolysis intervention. Feasibility will be assessed by the extent of protocol completion and myocardial visibility. Efficacy will be determined by angiographic patency rate, ST-elevation resolution, infarct size and left ventricular volumes, and function measured with cardiovascular magnetic resonance imaging, and contrast and strain echocardiography. A comparison will be made with matched controls using an existing STEMI database.

**Discussion:**

Sonothrombolysis is a novel technique for the treatment of cardiovascular thromboembolic disease. The first clinical trials on its use for STEMI have demonstrated promising results. This study will be the first to examine the feasibility of in-ambulance sonothrombolysis for STEMI.

**Trial registration:**

EU Clinical Trials Register (identifier: 2019-001883-31), registered 2020-02-25.

## Background

ST-segment elevation on the electrocardiogram (ECG) indicates the occlusion of an epicardial coronary artery, most commonly due to thrombus formation at the site of a ruptured atherosclerotic plaque. The optimal treatment strategy for ST-elevation myocardial infarction (STEMI) is immediate restoration of epicardial coronary blood flow. Currently, primary percutaneous coronary intervention (PCI) with concomitant dual antiplatelet therapy and periprocedural anticoagulation constitutes the treatment of choice in STEMI patients [1]. While successful reperfusion has led to a marked decrease in annual deaths over the past decades, long-term mortality and morbidity remain substantial [2, 3]. In addition to prolonged ischaemia and subsequent infarct size, microvascular injury due to ischaemic and reperfusion processes is a major determinant of adverse left ventricular remodelling and poor prognosis [4] and occurs in up to 50% of the patients [5]. By minimising infarct size and microvascular injury, left ventricular function may be preserved with improved long-term prognosis. Several studies have focused on early therapeutic interventions for reduction of infarct size and microvascular injury. Early drug therapy strategies include the use of low-dose fibrinolysis [6, 7], beta-blockers [8], adenosine [9], cyclosporine [10] and complement inhibition [11]. No or only small beneficial effects in a selected patient population have been demonstrated. Other interventions such as thrombus aspiration to reduce distal embolisation [12] and remote ischaemic conditioning [13] to reduce the possible detrimental effects of spontaneous reperfusion likewise did not improve outcome. A growing number of studies on adjunctive therapies for STEMI are performed in the pre-hospital setting. The time from STEMI diagnosis to PCI provides a window of opportunity for early therapy. A summary of recent studies on pre-hospital therapeutic strategies before PCI to reduce infarct size in STEMI patients and improve clinical outcomes is listed in Tab. 1. Recently, sonothrombolysis has been proposed as an adjunctive therapy for acute myocardial infarction [14]. In-vitro studies and in-vivo STEMI models have shown the potential of sonothrombolysis for restoration of epicardial and microvascular flow [15]. A recent randomised controlled trial on the effects of pre- and post-PCI sonothrombolysis in STEMI patients demonstrated a higher angiographic recanalisation rate prior to PCI and reduced infarct size in the intervention group [16]. Pre-PCI sonothrombolysis was performed at the emergency department in the hospital and resulted in thrombolysis in myocardial infarction (TIMI) flow grade ≥2 in almost half of the patients. By performing sonothrombolysis even before hospital arrival, its efficacy may be further improved. In this study, safety and technical feasibility of sonothrombolysis in STEMI patients in the pre-hospital ambulance setting will be assessed. To our knowledge, this is the first time that therapeutic echocardiography will be used in the ambulance.

**Table 1 Tab1:** Summary of recent randomised controlled trials on pre-hospital therapeutic strategies before PCI in patients with acute myocardial infarction

Therapy	Study	No. of patients	Primary endpoints	Outcome
Abciximab	Pels et al. (2008) [34]	101	STR before PCI Initial TIMI 3 flow in IRA	No improvement in initial TIMI flow or STR
	Petronio et al. (2012) [35]	110	Infarct size (LGE-MRI)	No reduction in infarct size
	Ohlmann et al. (2012) [36]	256	Complete STR (>70%) after PCI	No improvement in STR
Tirofiban	Van ’t Hof (2008) [37]	984	Mean residual STD after PCI	Improvement in STR
	El Khoury et al. (2010) [38]	320	Initial TIMI 2/3 flow in IRA	No improvement in initial TIMI 2/3 flow
Clopidogrel	Zeymer et al. (2012) [39]	337	Initial TIMI 2/3 flow in IRA	No improvement in initial TIMI 2/3 flow
Ticagrelor	Montalescot et al. (2014) [40]	1862	Initial TIMI flow STR before PCI	No improvement in initial TIMI flow or STR
Bivalirudin	Steg et al. (2013) [41]^a^	2218	Combined endpoint of death or major bleeding (30 days)	Reduced composite endpoint (driven by less major bleeding), increased stent thrombosis
Tenecteplase	Armstrong (2006) [42]	304	Combined endpoint of death, re-infarction, refractory ischaemia, congestive heart failure, cardiogenic shock, and major ventricular arrhythmia	No difference in combined endpoint compared with PCI alone
	Thiele et al. (2011) [43]	162	Infarct size (LGE-MRI)	No reduction in infarct size
Metoprolol	Ibanez et al. (2013) [44]^a^	270	Infarct size (LGE-MRI)	Reduction in infarct size
	Roolvink et al. (2016) [8]	684	Infarct size (LGE-MRI)	No reduction in infarct size
Oxygen	Stub et al. (2015) [45]	441	Infarct size (enzymes)	Increase in infarct size
	Khoshnood et al. (2018) [46]	95	Myocardial salvage index (LGE-MRI)	No improvement of myocardial salvage
Ischaemic conditioning	Hausenloy et al. (2019) [47]^a^	5115	Combined endpoint of cardiac death and HF hospitalisation	No improvement of clinical outcomes
Hypothermia	Testori et al. (2019) [48]	101	Myocardial salvage index (LGE-MRI)	No improvement of myocardial salvage

*LGE-MRI* late gadolinium enhancement—magnetic resonance imaging, *TIMI* thrombolysis in myocardial infarction, *STR* ST-segment resolution, *STD* ST-segment deviation, *PCI* percutaneous coronary intervention, *IRA* infarct-related artery, *MACE* major adverse cardiac events, *HF* heart failure

^a^Some patients received treatment during transfer to the PCI centre, others received the treatment upon arrival in the hospital

## Methods

### Objectives

The primary objective is to study safety and feasibility of sonothrombolysis application in the ambulance. The secondary objective is to evaluate the efficacy of in-ambulance sonothrombolysis as assessed by ST-elevation resolution, initial angiographic patency, infarct characteristics and left ventricular dimensions, function, perfusion and remodelling.

### Endpoints

The main endpoints are safety and practical feasibility. Safety will be assessed by the occurrence of ventricular arrhythmias defined as sustained ventricular tachycardia and/or ventricular fibrillation and the occurrence of shock defined as a systolic blood pressure <100 mm Hg in combination with tachycardia (heart rate >100/min), after initiation of sonothrombolysis and before PCI.

These endpoints will provide relevant information regarding the safety of sonothrombolysis in the ambulance. Two forms of shock are relevant for the present study: anaphylactic shock (very rare in case of commercially available microbubbles, 1:10,000–100,000) and cardiogenic shock. The incidence of cardiogenic shock in STEMI patients is around 7% [17]. The incidence of ventricular arrhythmias in STEMI patients before percutaneous coronary intervention is around 3% [18]. It is important to note that some ventricular arrhythmias, e.g. runs of ventricular premature complexes or accelerated idiopathic ventricular arrhythmias, are not uncommon after flow restoration in STEMI and are even related to improvement of myocardial perfusion [19].

Practical feasibility will be assessed by the extent of sonothrombolysis completion during ambulance transfer. The ultrasound images will be saved for offline review; sonothrombolysis completion will be measured by counting the number of high mechanical index impulses applied in each view and the quality of the acquired apical views will be scored.

Secondary endpoints are ST-elevation resolution, initial TIMI flow, infarct characteristics and left ventricular dimensions and function at baseline (3–5 days) and follow-up (6–8 weeks) with cardiovascular magnetic resonance imaging (CMR). Myocardial perfusion and left ventricular remodelling parameters will be assessed on follow-up contrast-enhanced echocardiography (3–4 months). Six-month event-free survival will be calculated from treatment initiation to 6 months afterwards, where events include death, congestive heart failure, life-threatening arrhythmias, recurrence of acute coronary syndrome and need for prophylactic defibrillator.

### Patient enrolment

This study will be conducted in accordance with the standards for Good Clinical Practice and the Declaration of Helsinki. Ethics approval was obtained on 3 February 2020 from the Medical Ethics Review Committee VUmc (reference: 2019.556—NL69980.029.19). Given the logistical challenge of the study and the primary aim to assess feasibility, a total of ten patients will be included. Due to the urgent setting and need for rapid initiation of the study protocol, only brief oral consent will be obtained. The written informed consent procedure will be deferred until after coronary angiography. Inclusion and exclusion criteria are listed in Tab. 2. All patients will receive drug therapy consisting of dual antiplatelet therapy (DAPT) and intravenous heparin in the ambulance. DAPT will be continued for 1 year according to current guidelines.

**Table 2 Tab2:** Eligibility criteria

Inclusion criteria	– Acute (within 12 h) or worsening chest pain or shortness of breath associated with >1.0 mV ST elevation on the ECG in at least 2 contiguous leads – Age ≥30 years – Adequate apical and/or parasternal images by echocardiography
Exclusion criteria	– Previous coronary bypass surgery – Cardiogenic shock – Known or suspected hypersensitivity to ultrasound contrast agent used for the study – Known bleeding diathesis or contraindication to glycoprotein IIB/IIIA inhibitors, anticoagulants or aspirin – Known large right to left intracardiac shunts

**Fig. 1 Fig1:**
[figure not shown]
Study flow chart. (*STEMI* ST-elevation myocardial infarction, *EMS* emergency medical services, *CAG* coronary angiography, *PCI* percutaneous coronary intervention)

**Fig. 2 Fig2:**
[figure not shown]
Portable ultrasound system mounted inside the ambulance enables diagnostic and therapeutic echocardiography (sonothrombolysis) during patient transfer to the PCI centre

At least three ECGs will be performed: before and after sonothrombolysis and after primary PCI. Absolute and relative cumulative ST-elevation resolution will be measured. Creatine kinase (CK), creatine kinase MB (CK-MB) and troponin levels will be obtained through standard care venous blood sampling in the hospital. Maximum biomarker levels will be reported.

All patients will undergo invasive coronary angiography. Primary PCI will be performed according to the guidelines and at the discretion of the interventional cardiologist. TIMI flow grade before and after PCI, myocardial blush grade and thrombus burden will be reported.

CMR imaging will be performed at baseline (3–5 days after presentation) and 6 to 8 weeks later. A clinical 1.5 or 3.0 T scanner with phased-array cardiac receiver coils will be used. Cine images are obtained using a steady state free precession sequence in three long-axis views and multiple short-axis views to examine left ventricular mass, function and volumes and to quantify left ventricular ejection fraction. T2-weighted images will be taken in short-axis planes identical to the cine images. T1 mapping in three parallel short-axis views positioned at the basal, mid and apical levels will be done using a Shortened Modified Look-Locker Inversion recovery sequence. First-pass perfusion will be performed in the same three short-axis views as T1 mapping using saturation recovery imaging. Early and late gadolinium enhanced (LGE) images are acquired 2 and 10 min, respectively, post-injection using a segmented gradient echo sequence. LGE images will be used to assess infarct size, the presence and extent of microvascular injury and to measure the area at risk. Short-axis T2-weighted images will be used for the detection of intramyocardial haemorrhage and infarct-related oedema. All CMR analyses will be performed in a core laboratory by blinded observers.

Contrast-enhanced echocardiography will be performed 3–4 months after initial presentation. Left ventricular function and volumes will be measured. Left ventricular remodelling will be defined as a 20% increase in end-diastolic volume at the 3 month follow-up biplane contrast-enhanced echocardiogram compared with the pre-discharge echocardiogram.

Follow-up will take place at 6 months by telephone contact and electronic patient records will be consulted.

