### Statistical analysis

Statistical analyses for the primary endpoints will be purely descriptive. Baseline characteristics will be presented, continuous variables will be given as *n* (%) and mean with interquartile range (IQR). Secondary outcomes will be compared between patients included in this study and historical control patients. All these analyses will be considered exploratory. Categorical variables will be compared between groups using a chi-square test or Fisher’s exact test. Continuous variables will be compared using an independent sample t‑test (if normally distributed) or the Mann-Whitney test (otherwise). The study and the trial conduct will be audited by an independent monitor from the Amsterdam UMC.

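### Absolute ST-elevation resolution is compared with historical controls by an unadjusted two-sample test, so a difference in starting ST elevation can appear as a treatment effect

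*Protocol article*

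**What the plan says.** The Endpoints section puts ST-elevation resolution first among the secondary outcomes: "Secondary endpoints are ST-elevation resolution, initial TIMI flow, infarct characteristics and left ventricular dimensions and function". Study procedures (text after Figure 2) gives the measurement schedule, "At least three ECGs will be performed: before and after sonothrombolysis and after primary PCI", and the outcome: "Absolute and relative cumulative ST-elevation resolution will be measured".

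The Statistical analysis section fixes the comparison: "Secondary outcomes will be compared between patients included in this study and historical control patients". For the test it says "Continuous variables will be compared using an independent sample" t-test if the data are normal, and Mann-Whitney otherwise. No covariate is named. The same section labels all of these analyses exploratory and the primary analysis descriptive.

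The abstract adds: "A comparison will be made with matched controls using an existing STEMI database". It gives neither matching variables nor a matching ratio. On size, "a total of ten patients will be included", justified as follows: "Given the logistical challenge of the study and the primary aim to assess feasibility". No power, significance level or effect size is stated.

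**The concern.** Absolute resolution is the starting cumulative ST elevation minus the later one. A patient who starts with more ST elevation has more to lose, so the group that starts higher tends to show the larger absolute fall even if treatment does nothing.

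Randomisation would make such a difference a matter of chance. Here the treated patients come from one equipped ambulance and must have adequate echocardiographic images, while the controls come from a database. The named tests have no place for the starting value, although resolution cannot be calculated without it. At stake is whether the absolute-scale estimate, one of the efficacy signals a later trial might draw on, reflects treatment or case mix. A second, smaller matter is that a raw change score can be less precise than a baseline-adjusted comparison.

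**Working it through.** The plan has no figure of its own to reproduce. Only the ten treated patients come from the document. Everything else is assumed:

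- 10 or 40 controls, two-sided 5% level.
- Starting cumulative ST elevation gamma-distributed, mean 10 mm in controls, coefficient of variation about 0.5 (0.4 to 0.6 tried).
- Fraction resolved: mean 0.5, SD 0.25, the same in both groups, so no treatment effect.
- Treated group's starting values multiplied by 1.2 or 1.4.
- For precision: pre/post correlation ρ from 0.3 to 0.8, and a true effect of 1 SD.

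**Size of the spurious difference.** Write absolute resolution as A = f × B, where f is the fraction resolved and B the starting value. The expected group difference is 0.5 × (mean B treated − mean B control).

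- 20% higher: 0.5 × (12 − 10) = 1 mm.
- 40% higher: 0.5 × (14 − 10) = 2 mm.

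Relative resolution is A / B = f, so its expected difference is 0.

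**False-positive rates (simulation with no true effect).**

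| Analysis | 10 v 10, +20% | 10 v 10, +40% | 10 v 40, +20% | 10 v 40, +40% |
|---|---|---|---|---|
| Absolute, pooled t-test | 7-8% | 14-15% | 13-14% | about 31% |
| Absolute, Welch t-test | – | – | about 6% | about 13% |
| Relative, t-test | about 5% | about 5% | about 5% | about 5% |
| Baseline-adjusted model | about 5% | about 5% | 7-8% | about 8% |

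Mann-Whitney does not cure the problem: at the 40% shift it gives 11-15% (10 v 10) and 17-24% (10 v 40). The Welch row shows that much of the excess at 10 v 40 is not baseline bias. Scaling up the smaller group also raises its variance, which a pooled t-test handles badly when group sizes differ.

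**A second model.** If the later value depends linearly on the starting value with correlation ρ and equal variances, an imbalance of δ SD shifts the unadjusted change by (1 − ρ)δ. For δ = 1 that is 0.7, 0.5 and 0.3 SD at ρ = 0.3, 0.5 and 0.7, with t-test false-positive rates of 23%, 20% and 14% (10 v 10). Adjustment brings the bias to about 0 and the rate to 4-6%.

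**Precision.** The change score has variance 2(1 − ρ)σ² and the adjusted outcome (1 − ρ²)σ², a ratio of (1 + ρ)/2. At ρ = 0.5 these are 1.0σ² and 0.75σ². For 10 v 10 and a 1 SD effect:

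- Change score: noncentrality 1/√(1.0 × 0.2) = 2.24, 18 df, power 56%.
- Adjusted: 1/√(0.75 × 0.2) = 2.58, 17 df, power 68%. With the small-sample factor 1 + 1/16 it is 66%.

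Without that factor the gain is 17 points at ρ = 0.3, 6 at 0.7 and 2 at 0.8 (1 with the factor). These figures assume balanced baselines. With a 0.8 SD imbalance the adjusted and unadjusted powers are about 59% v 56% at ρ = 0.5, 76% v 78% at ρ = 0.7, and 88% v 92% at ρ = 0.8.

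**The case against.** The case on the other side is substantial.

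- **The plan already has a baseline-normalised form.** A reader might infer that the whole ST-resolution comparison is biased. The documents do not support that: relative resolution is planned too, and under proportional resolution it stays near 5% at every shift. This stands and confines the point to the absolute scale.
- **The controls are described as matched.** Close matching on starting ST elevation would remove most of the bias. A condensed article may leave the matching variables to the full protocol, so their absence is not itself a fault, and one should not infer that starting ST elevation was ignored. Equally, the article gives no ground to assume it was used, and the named independent-sample tests make no use of matching.
- **Bias and lost precision do not both occur at full size.** A reader might infer that the unadjusted test always wastes information. The precision gain is clear only when baselines are roughly balanced. It shrinks or reverses under strong imbalance or high ρ.
- **The large rates with 40 controls overstate the bias.** The document does not fix the variance form of the t-test, and Welch removes much of the excess.
- **The stakes are low.** The comparison is exploratory, and no decision rule, significance level or power attaches to it. That stands, but it does not make a confounded estimate more useful.
- **Control ECG timing is not documented.** A covariate cannot repair ECGs taken at different times.

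**Conclusion.** The point holds for absolute resolution only, as a minor improvement to a method the article states. The named tests leave the starting value out of a comparison between non-randomised groups, on an outcome that scales with it.

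If the treated group starts 20% or 40% higher, about 1 or 2 mm of apparent benefit arises with no effect, and the nominal 5% error rate becomes roughly 7-8% or 14-15% with 10 controls. A group that starts lower would hide benefit by the same mechanism. These sizes rest wholly on assumed imbalance, spread, resolution fraction and control numbers. If matching on starting ST elevation is close, the bias is small and the remaining argument is precision. Baseline adjustment does not address confounding by calendar time or patient selection, which remains whatever the test. The descriptive primary analysis is unaffected.

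**What to change.** In the Statistical analysis section, for absolute ST-elevation resolution, replace the two-sample test with a linear model of the later cumulative ST elevation on group, with cumulative ST elevation on the first ECG as covariate. Report the adjusted difference with a 95% interval, labelled exploratory. Modelling the fall instead of the later value gives the same group difference with the sign reversed.

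Keep the planned between-group comparison of relative resolution. It was the better-behaved analysis in the proportional model with 40 controls (about 5% against 7-8% for the adjusted model) and should not be reduced to a summary.

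Do not extend the adjustment to the CMR scan at 3-5 days. The article calls it baseline, but it is made after treatment, and conditioning on it could remove part of the effect.

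The cost is one or two sentences, one degree of freedom, and a roughly linear relation to be checked by plot. No new measurement is needed where resolution can be computed in both groups, but the control ECGs must have been taken at comparable times, and this should be confirmed in the database before the comparison is made.

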### Statistical analysis

Statistical analyses for the primary endpoints will be purely descriptive. Baseline characteristics will be presented, continuous variables will be given as *n* (%) and mean with interquartile range (IQR). Secondary outcomes will be compared between patients included in this study and historical control patients. All these analyses will be considered exploratory. Categorical variables will be compared between groups using a chi-square test or Fisher’s exact test. Continuous variables will be compared using an independent sample t‑test (if normally distributed) or the Mann-Whitney test (otherwise). The study and the trial conduct will be audited by an independent monitor from the Amsterdam UMC.

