## Discussion

Thrombolysis and PCI have significantly improved the prognosis of STEMI patients. However, two major clinical problems remain. Firstly, early reperfusion is restricted by patient factors, delays in transfer to PCI capable centres and delays in PCI initiation [1]. The longer the ischaemic time, the greater the size and transmurality of the infarct zone [21, 22]. Actions have been taken to reduce ischaemic time by facilitating early STEMI diagnosis and prehospital activation of the cardiac catheterisation lab. However, total ischaemic time in STEMI patients remains substantial [23]. Secondly, although successful epicardial revascularisation may be achieved, up to 50% of the patients exhibit microvascular injury, resulting in higher infarct sizes, adverse left ventricle remodelling and worse prognosis [4]. Novel therapeutic interventions for STEMI should preferably be applied within minutes of STEMI diagnosis and should also treat or prevent microvascular injury.

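### The planned independent-sample, unadjusted tests neither carry through the matching of controls promised in the abstract nor correct for a residual imbalance in ischaemic time

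*Protocol article*

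**What the plan says.** The Methods paragraph of the abstract says of efficacy: "A comparison will be made with matched controls using an existing STEMI database". The Statistical analysis section describes the same comparison without mentioning matching: "Secondary outcomes will be compared between patients included in this study and historical control patients". It then fixes the tests. For categorical outcomes: "Categorical variables will be compared between groups using a chi-square test or Fisher’s exact test". For continuous outcomes: "Continuous variables will be compared using an independent sample t‑test (if normally distributed) or the Mann-Whitney test (otherwise". No covariate, matched set or pairing enters any of them. The section limits what may be claimed: "All these analyses will be considered exploratory", and the primary endpoints are only described, without controls.

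The secondary endpoints include infarct characteristics and left ventricular dimensions and function on CMR (Endpoints). On what drives infarct size, the Discussion says: "The longer the ischaemic time, the greater the size and transmurality of the infarct zone". The sample size is a feasibility choice: "Given the logistical challenge of the study and the primary aim to assess feasibility, a total of ten patients will be included".

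**The concern.** The comparison is not randomised, so its credibility rests on how the controls are made comparable and on whether the analysis uses that. The abstract supplies a design-stage safeguard, matching, and the analysis section then treats the two groups as independent samples. Two things can go wrong.

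First, if matching makes the members of a matched set alike, an independent-sample test overstates the standard error and loses sensitivity, which ten treated patients can ill afford.

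Second, if matching leaves a difference in ischaemic time, none of the listed tests can remove it, and on the article's own account that difference would appear as a difference in infarct size. Entry is open up to 12 h from onset (Table 2), so delay can vary widely. The treated patients also come through one equipped vehicle, with an ECG sent ahead and a ride of roughly 10–15 min (Study procedures, Challenges).

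At stake is how the exploratory infarct-size and ventricular-function results can be read. The safety and feasibility conclusions are not affected.

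**Working it through.** **No figure to reproduce.** The article gives no number of controls, matching ratio, SD, effect size or power for this comparison. Ten treated patients is the only numerical input from the document. Everything else below is an assumption chosen to show a range.

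**Case A: 1:1 matching works.** Assume ten pairs, common SD σ, within-pair correlation ρ and no treatment effect.
- Variance of the mean difference assumed by the independent t-test: 2σ²/10.
- True variance: 2σ²(1 − ρ)/10.
- The standard error is therefore too large by about 1/√(1 − ρ): 1.20 at ρ = 0.3 and 1.41 at ρ = 0.5.

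Simulated type I error at a nominal two-sided 5%:

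| ρ | Independent t-test | Paired t-test |
|---|---|---|
| 0 | about 5% | about 5% |
| 0.3 | about 2.2% | about 5% |
| 0.5 | about 0.9% | about 5% |

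**Case B: delay stays unbalanced.** Assume a correlation r between ischaemic time and infarct size of 0.3 to 0.5, a group difference d in ischaemic time of 0.25 to 0.75 SD, and no treatment effect.
- Spurious difference in infarct size = r × d. Low end: 0.3 × 0.25 = 0.075 SD. High end: 0.5 × 0.75 = 0.375 SD.
- Noncentrality with m controls = (r × d)/√(1/10 + 1/m). At m = 40 the root is 0.354, giving 0.21 to 1.06 on 48 degrees of freedom. At m = 10 it is 0.447, giving 0.17 to 0.84 on 18 degrees of freedom.
- Rejection rate of the nominal 5% test: 5.5% to 18.0% at m = 40, and 5.3% to 12.5% at m = 10.

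**Scale.** The 95% CI half-width for the difference is t(0.975) × √(1/10 + 1/m): 2.101 × 0.447 = 0.94 SD with 10 controls and 2.002 × 0.346 = 0.69 SD with 50. The assumed bias of 0.075 to 0.375 SD is smaller than the sampling uncertainty throughout.

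**Does adjustment work at this size?** In a simulation at the high end of Case B (r = 0.5, d = 0.75), linear regression on group and the one covariate brought type I error from about 18% to 5.0% (10 v 40) and from about 12–13% to 5.1% (10 v 10). This assumes that the covariate is the confounder and acts linearly.

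**The case against.** The strongest reply is that matching is itself a control for confounding, and the article says controls are matched. The matching variables are not named, but a condensed article may leave them to the full protocol, so they could include delay or infarct location. That stands. A reader might infer that the comparison is wholly uncontrolled, and the documents do not support this. The reply does not rescue the stated tests, because successful matching is exactly the case in which an independent-sample test is the wrong one.

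A reader might also infer that historical controls had longer delays, since the Discussion says: "Actions have been taken to reduce ischaemic time by facilitating early STEMI diagnosis and prehospital activation of the cardiac catheterisation lab". The documents do not establish this. The next sentence there says total ischaemic time remains substantial, and nothing dates the database or describes its patients' transfer. The direction and size of any imbalance are unknown.

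The exploratory label also counts. It limits the claims and lowers the importance of the point, but it does not make the estimate unbiased or its interval correct.

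Two objections to adjustment have force. Cath-lab activation, an ECG sent ahead and a short ride act mostly after the diagnostic ECG, so onset-to-ECG time cannot remove differences arising later. And the article does not name culprit artery or infarct location as a determinant of infarct size, so that covariate is a suggestion from outside the text. Nor does anything say that the database holds onset time. Regression on several covariates would be strained with ten treated patients. One or two, fitted on treated and controls together, is workable, and a matched analysis is an equally good route.

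Blinded core-laboratory CMR reading protects against reading bias, not against this.

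**Conclusion.** The point holds as a mismatch between design and analysis. The abstract promises matched controls, while the Statistical analysis section fixes tests that ignore matching and cannot adjust for the one determinant of infarct size that the article itself names. The stated test is conservative if 1:1 matching succeeds and anti-conservative if delay remains unbalanced. The sizes in the working are illustrations that rest on assumed correlations, imbalances and control numbers; at the low end of Case B the inflation is trivial.

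The documents do not support saying that a spurious treatment effect is likely, or that it would favour sonothrombolysis. The comparison is secondary and exploratory, so this is a modest improvement that should be made. It does not threaten the trial's primary aim.

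**What to change.** In the Statistical analysis section, for infarct size, ejection fraction and ventricular volumes:

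- Replace the independent-sample tests as the main comparison with one of two analyses. Either respect the matching (paired, or stratified by matched set), or fit a linear regression on group adjusted for time from symptom onset to diagnostic ECG and, where the database holds it, infarct location. Adjustment is not needed for variables that are already matching factors.
- Use onset-to-ECG rather than onset-to-PCI time, because it precedes treatment and so does not adjust away a delay that the treatment causes. Show ECG-to-reperfusion time by group, since the adjustment does not cover it.
- Select controls before their outcomes are seen.
- Report the difference with a 95% CI, labelled exploratory, and keep the unadjusted tests as descriptive support.

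The cost is a change of wording and, if the fields exist, extraction of one or two variables from the control database. Controls with unknown onset time would drop out or need a sensitivity analysis, and the regression uses one or two degrees of freedom.
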